**Fig 2 pone.0325558.g002:**
[figure not shown]
Outcomes and data gathering timeline. CEO-MHS = Consumer Evaluation of Mental Health Services; EI = emotional intelligence; eMeds = electronic medication management system; IMI = intramuscular injection; ims+ = incident management system; ProQOL = Professional Quality of Life; VPC-M-FR = Modified Violence Prevention Climate.

There will be three forms of comparisons within the current evaluation. Between- i) and within-group ii) comparisons will be applied to test the first and second sets of hypotheses. The third will be a between-cluster comparison iii), intended to identify the most active co-occurring therapeutic and nursing responses (clusters) contributing to the Safe Steps’ overall impact. The first set of hypotheses is that implementation units will exhibit greater reductions in the IRR for restrictive practice events, the estimate of restrictive practice duration, and the IRR for physical injuries, compared to control groups and their baseline levels. The second set of hypotheses is that measures of service experience, perceived staff action towards violence prevention, nurses’ professional quality of life, and nurses’ perceived demonstration of emotionally intelligent workplace behaviours at the final time point would be significantly higher than at baseline. The between-group comparisons will be conducted exclusively to address the first objective, as these analyses will depend on accessible routine reports on restrictive practices and physical injuries selected for this purpose. Australian public acute mental health services are legally mandated to report on seclusion and physical restraint events and duration as key performance indicators [52]. Events of physical injuries and sedation via IMI are also routinely documented in established information management systems. These routine measures will help minimise performance and detection bias associated with the lack of blinding. Conversely, conducting a between-group comparison on non-routine measures could be cost-prohibitive and challenging to implement, as exemplified by unmet sample size requirements in previous studies [27]. This evaluation will have no randomisation, although covariate balancing will be applied to between- and within-group comparisons in testing the first set of hypotheses.

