### Recruitment and consent

The current evaluation will employ various recruitment strategies, with consent procedures tailored to each data collection activity. The implementation of Safe Steps follows an opt-in model, with recruitment proceeding through an asynchronous, multi-centre approach [65]. Each site independently decides when to implement Safe Steps, allowing for autonomy and flexibility, while ensuring consistency in the intended intervention across settings. Recruitment began at the first intervention site on 1st March 2024, with the latest site starting on 16th April 2024. Baseline data collection for the unit register, ims+, and eMeds data, covering the year before each site’s recruitment start date, commenced alongside recruitment. The final recruitment and data collection will conclude one year after the latest recruitment start, on 15th April 2025. At the time of the initial submission of the protocol for publication consideration, the study has reached its third time point.

For event-based analyses, the consent to access administrative data from unit registers and incident management systems was waived, because individual and nurse participant identifiers will not be gathered, nor will the data be re-identifiable. On the other hand, completion of the de-escalation log will serve as implied consent, and no identifying nurse details will be recorded. Identifying individual information will be gathered solely to help complete the logs, after which it will be removed and replaced with a randomly assigned study code before being shared with the first author.

For survey-based measures, peer worker-led surveys will be open to individuals over 18 who can consent to participate in the research. The only exclusion criteria are individuals receiving care with an identified need for an interpreter who refuse to use interpretation services adjacent to the unit. Increasing access to research participation with interpretation services was done with the consideration of guidance from the state-wide service that streamlines care pathways for culturally and linguistically diverse (CALD) individuals.

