#### Mental health nursing de-escalation logs.

The mental health nursing de-escalation log developed by a clinician (MF) in collaboration with another clinician (AT) has five sections: i) incident details, ii) aggression type, iii) interventions, iv) situational aggression levels, and v) outcomes, covering 51 variables. It records contextual information (date, location, number of staff involved), direction of aggression (e.g., individual to nurse), and lists interventions like the four Safe Steps and other non-relational, non-coercive de-escalation techniques. Situational aggression levels are rated on a 6-point scale from calm to physical aggression with weapons. Outcomes include restrictive practice use (e.g., seclusion, physical restraint, sedation via intramuscular injections), Code Black, time out, care level allocation, physical injuries, and incident management system reporting. Nurses will be trained to complete these logs, which they will contemporaneously cross-reference with unit data to minimise recall bias. Concurrent validation of the restrictive practice use outcomes will be attempted.

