### Procedures

The participating nurses will receive the training programme component of the Safe Steps. Nurse educators will support the opt-in-based implementation of the three components of the Safe Steps, ensuring that it is an integrated aspect of everyday practice in providing acute mental health care. Regular meetings, site visits, posters on the intervention’s key values, pull-up banners, coffee vouchers, and cheat sheet cards on the four steps will be implemented to support intervention uptake. Changes in nursing practices and measures of individual and nurse participants’ outcomes and experiences in the intervention sites will be collected over two years at various time points (see Fig 2). Restrictive practice and physical injury outcomes will be gathered prospectively from both intervention sites and control groups from administrative records, except for the de-escalation log. Outcomes from standardised measures and qualitative data will be collected prospectively only from people receiving care and nurse participants in the intervention sites. Data collection may cease due to unforeseen circumstances, such as reinstated COVID-19 restrictions.

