### Analysis plan

Quantitative and qualitative analyses will be used to answer the evaluation’s objectives. Consultations with statisticians occurred for the range of statistical treatments employed in this evaluation. Various packages in R [74] and RStudio [60] will be maximised for the quantitative analyses, and Matplotlib [75] will be utilised for visualising outcomes. Each hypothesis will be supported if outcomes are statistically significant at p < .05.

Poisson mixed-effects models [56] will be used for count data and linear regression models for continuous outcomes, to determine whether these outcomes differ according to intervention implementation and time points. Data cleaning and validation, assumption checks, model diagnostics, and follow-up analyses will be undertaken. Negative binomial mixed models, zero-inflated models, and linear mixed-effect models may be used depending on the model’s diagnostics. Covariates in the mixed-effect models will include the acute care unit, calendar month, day, year, and the day within the study period for each daily event aggregate. Model selection will prioritise parsimony and explanatory strength. Inverse probability weighting (IPW) will be applied in the between- and within-group comparisons. Using the ipw package [76], IPW will be used to balance covariates, including but not limited to the average harm scores of daily aggregates, the number of high observation beds, the number of seclusion rooms, and other confounds (i.e., physical restraint and Code Blacks are closely interrelated, influencing each other’s occurrence or implementation [77]). Listed covariates for balancing will be used, subject to the data’s fit and the statistical model’s ability to achieve convergence in the IPW approach.

Hierarchical clustering analysis [78] will support the emergence of co-occurring mental health nursing response clusters, which will then be the fixed effect in modelling differential associations with restrictive practices, physical injuries, and situational aggression. This cluster and regression analysis constitutes the between-cluster comparison to identify the most active response clusters contributing most to Safe Steps’ overall impact.

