The Safe Steps evaluation is robust. It contributes to the limited knowledge base that discerns the most active co-occurring responses contributing to a programme or multi-component intervention’s overall impact. A significant limitation of complex interventions aimed at reducing restrictive practices is determining which elements contribute most to the effect, particularly as the impact of nurses’ therapeutic responses has not been evaluated in isolation. Rather, it is usual to see before-and-after evaluations of training interventions on these responses [see 29,88]. Moreover, control groups and statistical adjustments will be applied to address the absence of randomisation. Given that recruiting appropriate control groups and controlling for confounds is a well-documented challenge in acute care reform [26], this approach that balances covariates enhances this evaluation’s validity. This evaluation includes outcomes, such as sedation via intramuscular injection and physical injuries, that are rarely examined in de-escalation training interventions [29], helping to expand understanding of key indicators for evaluating mental health service performance in Australia [90]. The Safe Steps implementation and evaluation features a year-long period, allowing for the identification of both emergent and sustained impacts. This extended timeframe contrasts with most Safewards studies, which typically span only a few months [27].

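### The between-cluster comparison is said to show which response clusters contribute most to Safe Steps' impact, but the stated model yields only associations among logged responses

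*Protocol article*

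**What the plan says.** The Design section (text after Fig 2) lists three forms of comparison. The third, between clusters, is "intended to identify the most active co-occurring therapeutic and nursing responses (clusters) contributing to the Safe" Steps' overall impact. The Analysis plan gives the method. Hierarchical clustering forms groups of co-occurring nursing responses, "which will then be the fixed effect in modelling differential associations with restrictive practices, physical injuries, and situational aggression". It then states the inference: "This cluster and regression analysis constitutes the between-cluster comparison to identify the most active response clusters contributing most to" Safe Steps' overall impact. The Discussion presents this as a strength of the evaluation: "It contributes to the limited knowledge base that discerns the most active co-occurring responses contributing to a programme" or multi-component intervention's impact. Its later paragraph on mechanisms repeats the aim.

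Three other places bear on the data behind this model:

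- The Measures section says the de-escalation log "lists interventions like the four Safe Steps and other non-relational, non-coercive de-escalation techniques".
- Procedures says restrictive practice and injury outcomes are gathered prospectively "from both intervention sites and control groups from administrative records, except for the de-escalation log".
- Recruitment and consent describes the baseline sources: "Baseline data collection for the unit register, ims+, and eMeds data, covering the year before each" site's start date. The log is not named there.

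The Abstract is more cautious. It lists the clusters under other outcomes and speaks only of their associations with outcomes.

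**The concern.** The protocol defines the impact of Safe Steps, for restrictive practices and injuries, as a greater reduction than in control units and than at the unit's own baseline. To say that a cluster contributed to that impact is therefore a statement about a difference between groups or periods. The cluster model as stated compares one set of logged responses with another, and neither comparator is written into it.

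The claim is also not tied to objective 1. If the controlled comparison showed no effect, the text would still allow the report to name the clusters that contributed to an impact that had not been shown. The Discussion offers this analysis as an answer to the field's difficulty in telling which elements of a complex intervention matter, so readers are likely to take the attribution at face value.

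**Working it through.** The plan gives no figure for this comparison, so there is nothing to reproduce. The check sets what the conclusion needs against what the stated model supplies.

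**Inputs stated for the cluster model**

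- *Exposure:* response cluster, formed from nursing responses. These are recorded in the de-escalation log (Measures).
- *Outcomes:* restrictive practices, physical injuries and situational aggression (Analysis plan).
- *Group or period contrast:* none stated.
- *Weighting:* inverse probability weighting is named for the between-group and within-group comparisons only.
- *Control-site logs:* not described. Procedures sets the log apart from the administrative records used at both kinds of site. Design confines between-group comparisons to objective 1 because they rely on routine reports.
- *Baseline logs:* not listed among the baseline-year sources.

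**What the conclusion needs**

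Take two clusters, A and B, with the logged episode as the unit (a simplification; the protocol does not state the unit for this model). In intervention units during follow-up, let w be the share of episodes handled with A, and let pA and pB be the risks of an outcome under each cluster. Let w0, pA0 and pB0 be the same quantities in the comparator (control units or baseline). The difference in risk per episode is

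[w·pA + (1 − w)·pB] − [w0·pA0 + (1 − w0)·pB0]
= (w − w0)(pA − pB) + w0(pA − pA0) + (1 − w0)(pB − pB0).

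The first term is the part due to a changed mix of responses. The other two are the parts due to a changed result within each cluster.

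**What the model supplies**

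The cluster model estimates pA − pB. The follow-up logs also give w. The comparator quantities w0, pA0 and pB0 need logs from control units or from baseline, and the documents describe neither as collected.

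**Consequence**

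If w = w0, pA = pA0 and pB = pB0, all three terms are zero and the programme has no effect per episode. Yet pA − pB can take any value. A large difference between clusters is thus compatible with no programme impact, and knowing that difference does not fix any cluster's share of an impact. This would hold even if every logged incident were equally severe, so it is separate from confounding by severity.

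**What a cluster contains**

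The log records the four steps and other de-escalation techniques together, and clustering is applied to nursing responses generally. A cluster may therefore contain few or none of the four steps. That does not make it irrelevant to the programme, but it does mean that its link to Safe Steps has to be reported and not assumed.

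**The case against.** The strongest reply is that this is explanatory work, reported in a condensed article. The cluster comparison is set apart from the two hypothesis sets, the Abstract calls it association, and the Discussion treats mechanisms of change as open questions to be explored qualitatively as well. Contrasts and reporting rules for a secondary analysis often sit in a separate analysis plan. All of that limits the weight of the point. It does not remove it, because the article itself states both the method and the inference, and the two do not match. The cautious wording elsewhere shows an inconsistency, and Design, Analysis plan and Discussion all keep the attribution.

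Several stronger readings are tempting and are not supported:

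- *The plan always declares a winner, or does so with a calculable false-positive rate.* The Analysis plan states no ranking rule and no significance trigger for clusters; its p < .05 criterion refers to hypotheses, and none is stated for clusters. It gives no number of clusters or logs and no event risks. Any error rate would rest on invented inputs and would move with the test chosen. A formal multiplicity correction is therefore not required by this point.
- *Baseline logs certainly do not exist.* That is inferred. Fig 2, which holds the data-gathering timeline, is not shown, and Procedures says changes in nursing practices are collected over two years. Even with baseline logs, no baseline contrast is stated for this model.
- *Period plays no part.* The calendar and study-day covariates listed for the mixed-effect models may extend to the cluster model. Adjusting for them is still not a contrast with baseline or control.
- *A cluster without one of the four steps should be excluded.* Safe Steps also includes training on wider engagement skills and review meetings that feed back successful responses, and Table 1 expects nurses to find other routes. Such a cluster could be a genuine programme pathway.

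**Conclusion.** The concern holds as a mismatch between a stated analysis and a stated conclusion. An association between response clusters and outcomes among logged episodes cannot apportion an effect that is defined against control units and baseline. As worded, the attribution could be made whether or not objective 1 shows an effect.

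The size is modest. One explanatory conclusion is affected, together with the Discussion's claim to identify the active responses. The effectiveness analyses under objective 1 and the survey hypotheses are untouched. No numerical error rate is claimed.

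The conclusion rests on reading the text as it stands, with no control or baseline contrast stated for the cluster model. The reading that logs are absent from control sites and from the baseline year supports it, but the conclusion does not depend on that reading.

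**What to change.** - In Design and Analysis plan, and in the matching statements in the Discussion, describe the result as an exploratory association between response clusters and outcomes among logged episodes. This agrees with the Abstract.
- Discuss a cluster as a possible contributor to Safe Steps' impact on an outcome only where the controlled effect on that outcome under hypothesis (a) has been shown.
- Keep situational aggression as an association only. It is not among the outcomes of hypothesis (a).
- For each cluster, report whether it contains Safe Steps elements, and which ones.

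This is a change of wording and needs no new data. The cost is that the attribution statement is unavailable if objective 1 is null.

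### Nursing-response clusters are ranked by their contribution to the programme's impact, but no incident-severity adjustment is assigned to that comparison, so clusters used in milder incidents can look beneficial

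*Protocol article*

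**What the plan says.** The Design section of the protocol article sets out three forms of comparison. The third is between clusters, "intended to identify the most active co-occurring therapeutic and nursing responses (clusters) contributing to the Safe Steps’ overall impact". The Analysis plan derives the clusters by hierarchical clustering of nursing responses, "which will then be the fixed effect in modelling differential associations with restrictive practices, physical injuries, and situational aggression". It then gives the purpose: "This cluster and regression analysis constitutes the between-cluster comparison to identify the most active response clusters contributing most to Safe Steps’ overall impact". The Discussion repeats that reading.

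Adjustment is described for the other two comparisons. The Analysis plan says: "Inverse probability weighting (IPW) will be applied in the between- and within-group comparisons". The Design section says that "covariate balancing will be applied to between- and within-group comparisons in testing the first set of hypotheses". The covariates listed for the mixed-effects models are unit, calendar terms and day within the study. The one covariate that resembles severity, a daily-average harm score, sits in the list for the weighting.

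The data come from the de-escalation log, whose five sections are "i) incident details, ii) aggression type, iii) interventions, iv) situational aggression levels, and v) outcomes". The log also records location, number of staff and direction of aggression, and it rates situational aggression on a 6-point scale. The section on the log does not say whether that rating is made before or after the nurse responds. The Analysis plan also provides for coding the triggers noted in the log, but only for the machine-learning feature analysis.

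**The concern.** This is confounding by indication. A nurse facing a person who is verbally distressed is unlikely to use the same mix of responses as a nurse facing physical aggression. The second incident is also more likely to end in seclusion, restraint, intramuscular sedation or injury, whatever the response. If cluster is modelled with only unit and time terms, the cluster coefficient mixes the effect of the responses with the severity of the incidents in which they were used.

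The wording raises the stakes. A table of associations would carry its own caution, but the plan says the result identifies which responses contributed most to the programme's impact. A service reading that could favour responses that happen to be used in easy incidents and discard those used in hard ones. The article's Introduction criticises earlier studies for leaving confounding unaddressed, and the Design section says accessible confounders will be balanced. The cluster comparison, as described, does not meet that standard.

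**Working it through.** The article gives no sample size, effect size or power figure for the between-cluster comparison, so there is no stated figure to reproduce. The check has two parts.

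**1. What is assigned to the cluster models**

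- Exposure: response cluster.
- Outcomes: restrictive practice, injury, situational aggression.
- Weighting and balancing: named for the between- and within-group comparisons only.
- Regression covariates: unit and time terms, which may also enter the cluster models.
- Incident severity or case mix: nothing assigned.

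**2. How large the distortion could be**

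All inputs below are assumptions at incident level; none is in the documents.

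*Scenario A: a cluster with no effect (true odds ratio 1).* Assume 40% of incidents are severe, and restrictive practice follows 10% of mild and 30% or 50% of severe incidents. The cluster is used in a share s of severe and m of mild incidents.

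- Severe share among incidents with the cluster: 0.4s / (0.4s + 0.6m)
- Severe share among incidents without it: 0.4(1−s) / [0.4(1−s) + 0.6(1−m)]
- Risk in each group: severe share × severe risk + (1 − severe share) × 0.10

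For s = 0.3 and m = 0.7, the severe shares are 0.12/0.54 = 0.222 and 0.28/0.46 = 0.609. With a severe risk of 30%, the risks are 0.222×0.30 + 0.778×0.10 = 0.144 and 0.609×0.30 + 0.391×0.10 = 0.222. The crude odds ratio is (0.144/0.856) / (0.222/0.778) = 0.59.

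| Cluster used in severe / mild incidents | Severe risk 30% | Severe risk 50% |
|---|---|---|
| 40% / 60% | 0.77 | 0.67 |
| 30% / 70% | 0.59 | 0.45 |
| 20% / 80% | 0.45 | 0.29 |

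This scenario shows spurious benefit. It does not show a reversed ranking.

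*Scenario B: a cluster that is truly better.* Let q be the severe share within a cluster, and let pL and pH be the risks in mild and severe incidents. Then

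crude RR = true RR × [qA·pH + (1−qA)·pL] / [qB·pH + (1−qB)·pL].

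With pL = 5%, pH = 40%, qA = 50%, qB = 30% and a true RR of 0.80, the crude RR is 0.80 × 0.225 / 0.155 = 1.16, so the better cluster looks worse. In a simulation of 200,000 incidents with these inputs, the unadjusted RR was 1.14 and the severity-adjusted RR was 0.79.

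*How much imbalance reverses the order?* Keep pL = 5% and qB = 30%, and set crude RR = 1: qA = [(qB·pH + (1−qB)·pL)/RR − pL] / (pH − pL).

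| Risk in severe incidents | True RR 0.70 | True RR 0.80 | True RR 0.88 |
|---|---|---|---|
| 15% | 64% | 50% | 41% |
| 25% | 54% | 44% | 38% |
| 40% | 49% | 41% | 36% |

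The 0.88 column corresponds to the 12% reduction in seclusion used in the Sample size section. It is borrowed here only for scale. At that size, a difference in severity mix of 6 to 11 percentage points is enough to reverse the order. With equal severity mix (30% in both), the crude RR equals the true RR and there is no bias.

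**The case against.** The strongest reply is that this is an omission in a condensed article. Calling cluster the fixed effect names the exposure; it does not say the models are otherwise unadjusted. The covariate list is open, and a fuller analysis plan may add severity terms. Part of this stands: a reader might infer that the cluster models are wholly unadjusted, and the article does not say so, since unit and time terms may enter. But the article places weighting and balancing with the other two comparisons, names situational aggression only as an outcome, and publishes the contribution reading. The point rests on those statements.

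Two further readings are tempting and should not be made.

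- A reader might infer that the article promises to explain the difference from the control sites. It speaks of overall impact, and the hypotheses test change against baseline as well as against control.
- A reader might take the cluster comparison as the study's main advance. The Abstract lists clusters among other outcomes, neither set of hypotheses concerns them, and the Discussion gives this as one strength among several.

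There are hedges: the Analysis plan speaks of associations, and the Discussion treats mechanisms of change as uncertain and open to qualitative study. Neither withdraws the claim about contribution.

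Two technical cautions also stand. The timing of the aggression rating is not stated, and number of staff may result from the response or from escalation, so either could be an unsafe adjuster. The unit of analysis is not stated for the cluster models either. The Sample section analyses restrictive practice and injury as daily aggregates, so the incident-level ratios above may not carry over directly.

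**Conclusion.** The point holds in a limited form. Followed as written, the between-cluster comparison yields a ranking open to confounding by incident severity and gives it a causal reading that associations within logs cannot carry. The direction and size of the bias are unknown. The illustrations rest on assumed risks and severity mixes, on responses being chosen partly by severity, and on incident-level analysis. They show that a null cluster can appear beneficial (crude odds ratio 0.29 to 0.77) and that reversal is possible under other assumptions. They do not show that either will happen here. The matter should be corrected, but it lies outside the study's two sets of hypotheses and does not affect the between- or within-group tests.

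**What to change.** 1. In every between-cluster model, adjust for or weight by log variables that are settled before the response: aggression type, direction of aggression, location and coded trigger, alongside unit and time.
2. State when the 6-point aggression level is rated. Add it as an adjuster only if the rating precedes the response, and never use the same rating as both adjuster and outcome.
3. Do not adjust for number of staff unless it is recorded before the response.
4. Replace the stated purpose, "to identify the most active response clusters contributing most to Safe Steps’ overall impact", with a description of which clusters are associated with restrictive practice, injury and aggression outcomes within logged incidents at intervention sites. Carry the same wording into the Design and Discussion sections. This change is needed whatever the adjustment, because type, direction, location and trigger may not capture severity fully.

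The cost is a few more parameters in each model and a more modest claim. The adjusters in step 1 come from the log, and coding of triggers is already planned, so no new data collection is needed for them.
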